## Abstract

**Background:**

Obesity is among the most significant health challenges facing today’s adolescents. Weight gain during adolescence is related to cardiovascular disease, type 2 diabetes, and some cancers in later life. Presently, adolescents living in Australia have limited access to age-appropriate obesity prevention services.

**Objective:**

This study aims to investigate whether a two-way text message program, with optional telephone health counseling, improves body mass index (BMI) *z* score and lifestyle outcomes in adolescents who are overweight.

**Methods:**

This study will be a single-blind randomized controlled trial (N=150) comparing a two-way text message intervention, with optional telephone health counseling, to usual care in adolescents (13-18 years old, inclusive) who are overweight (recruited from a pediatric weight management clinic and the broader community in Sydney, Australia). The intervention group will receive a six-month text message program, which consists of two-way, semipersonalized, lifestyle-focused text messages (four messages/week) in addition to usual care. The control group will be assigned to receive usual care. The study also includes a follow-up at 12-months. The primary outcome is a change in BMI *z* score at six months. Secondary outcomes are changes in waist-to-height ratio, diet, physical and sedentary activity levels, sleep quality, quality of life, self-esteem, self-efficacy, social support, and eating disorder and depression symptoms. Also, we will examine acceptability, utility, and engagement with the program through a study-specific process evaluation questionnaire, semi-structured telephone interviews, and an analysis of health counselor communication logs. The analyses will be performed by the intention-to-treat principle to assess differences between intervention and control groups.

**Results:**

The study opened for recruitment in December 2019. Data collection is expected to be completed by December 2021, and the results for the primary outcome are expected to be published in early 2022.

**Conclusions:**

This study will test the effectiveness of an interactive two-way text message program compared to usual care in improving BMI *z* score and lifestyle outcomes in adolescents with overweight. This interactive, innovative, and scalable project also aims to inform future practice and community initiatives to promote obesity prevention behaviors for adolescents.

**Trial Registration:**

Australia New Zealand Clinical Trials Registry (ANZCTR) ACTRN12619000389101; https://www.anzctr.org.au/Trial/Registration/TrialReview.aspx?id=377158&isReview=true

**International Registered Report Identifier (IRRID):**

DERR1-10.2196/16481

## Introduction

The global prevalence of obese and overweight adolescents has significantly increased over the last five decades, with 18% of the global population of children and adolescents being overweight or obesity in 2016 [1]. No developed countries have successfully halted the continuing upward trend in the prevalence of obesity and being overweight since 1980 [1]. For example, in 2017-2018, 25% of adolescents aged 12-17 years old and living in Australia, were overweight or obese [2]. Among older adolescents (16-17 years old) residing in Australia, there has been a 57% increase in the incidence of obesity in the last three years [2]. In the United States of America, 20.6% of adolescents aged 12-19 years old had obesity in 2013-2014 [3].

Preventing obesity during adolescence is important because adolescence is a life stage when risk factors and lifestyles are established [4,5]. Once obesity is established, weight loss and weight maintained after weight loss are difficult to achieve [6]. Consequently, gaining excess weight during adolescence is likely to lead to being overweight and obese in adulthood [7]. Weight gain during adolescence is associated with higher risk and earlier onset of cardiovascular disease [8], type 2 diabetes [9], and some cancers [10]. Moreover, adolescent obesity has adverse psychosocial outcomes, including weight stigma [11] and reduced quality of life and self-esteem [12]. Long term weight regulation is related to diet and physical behaviors that are adopted during adolescence and track throughout life [4]. Therefore, to halt the rise in the prevalence of overweight and obese adolescents, scalable, low-cost, and engaging strategies are needed.

Several lifestyle risk factors have been associated with excess weight gain during adolescence, and adolescents that are living in developed countries are not achieving national recommendations. Firstly, consuming the recommended intake of fruits and vegetables may prevent unhealthy weight gain [13], yet only 4% of adolescents living in Australia, aged 12-17 years old, meet national guidelines for fruit and vegetable intake [2]. Secondly, adolescents remain the highest consumers of discretionary foods and sugar-sweetened beverages, despite the evidence that consumption increases the risk of obesity and being overweight [14,15]. In Australia and the United States, over 60% of adolescents drink a sugar-sweetened beverage daily, adding 143 kilocalories per day. Moreover, discretionary foods account for a significant portion of adolescents’ total energy intake (>40% in Australian adolescents) [16]. Finally, short sleep duration [17], insufficient physical activity levels, and increased screen time are associated with an increased risk of obesity [18,19]. Both physical activity and sedentary screen-based behavior guidelines are met by less than 4% of adolescents aged 13-17 years old [20], and night-time technology use can have harmful effects on adolescent sleep duration [21].

Despite the apparent risk for weight gain during adolescence, evidence to inform effective interventions for this population is lacking. A 2019 Cochrane review of 31 randomized controlled trials (RCTs) testing the effectiveness of a range of interventions, which included diet or physical activity components or both, designed to prevent obesity in adolescents found limited effective interventions for adolescents aged 13-18 years old [22]. There has been more investment in childhood obesity prevention research, with over 85 RCTs conducted in children aged 6-12 years old. Moreover, the diet and physical activity strategies delivered to adolescents in the studies did not reduce their body mass index (BMI) *z* score, and there has been limited investigation of digital intervention modalities. Current attrition rates for traditional, in-person obesity prevention and management interventions in adolescents remain highly variable, with 27% to 73% of participants dropping out of interventions for reasons including the intervention not meeting the adolescent’s expectations [23,24]. Digital technology has been identified as an engaging intervention modality for overweight and obese adolescents [25]. Thus, mobile phone interventions hold promise for delivering interventions that are scalable, low-cost, and engaging.

Currently, over 90% of adolescents living in Australia and the United States own a mobile phone [26,27], and text messaging remains a primary means of communication between adolescents [27]. There is a small body of evidence which indicates one-way text message interventions can promote weight loss in adults [28]. Emerging research has shown that text messages are a feasible and acceptable form of communication in interventions for adolescents with obesity [29-32]. However, there is limited high-quality evidence for the role of two-way text messages to improve obesity prevention behaviors in adolescents who are overweight. Therefore, the primary aim of this study is to test the effectiveness of a two-way, semipersonalized text message program, with optional health counseling, compared to usual care for improving adolescents’ BMI *z* score. This study also aims to determine if the text message program can improve lifestyle outcomes. The study will also examine acceptability, utility, and engagement with the program.

## Methods

### Study Design

The TEXTBITES (TEXT message Behavioral Intervention for Teens on Eating, physical activity, and Social wellbeing) study is a single-blind, multi-center, randomized controlled trial, which delivers a six-month obesity prevention program via text messages to adolescents who are overweight. The study also includes a twelve-month follow-up (Figure 1). The sites include public hospitals and a pediatric weight management clinic at a public children’s hospital in Sydney, Australia. Participants will be recruited via referral from the pediatric weight management clinic, and from the local community via print and digital advertisements at community centers, high schools, and tertiary education providers. A log of all recruitment strategies utilized will be kept. The target sample size is 150 adolescents aged 13-18 years old inclusive, who are overweight. Participants will be randomly allocated to either a control or intervention group. The control group will be assigned to receive usual care. For this study, usual care is defined as accessing available health services and information for adolescent obesity prevention. The intervention group will be allocated to receive the six-month, two-way text message program for obesity prevention that provides practical tips and information, motivation, and support for lifestyle modification for healthy eating, physical activity, and mental wellbeing behaviors, in addition to usual care. Trained research personnel blinded to the group allocation will conduct assessments at baseline, six-, and twelve-months during a face-to-face interview.

**Figure 1 figure1:**
[figure not shown]
Flow chart of study design. Adolescent participants 13-18 years, with overweight are considered for inclusion in the study and randomization is single blind, with allocation determined and initiated by the computerized program.

### Randomization and Blinding

After obtaining written informed consent from adolescents and their parents or guardians (if <18 years old) and completing the baseline assessment, the research assistant will enter the data into a secure web-based database. Then randomization will occur via a centralized, computerized randomization program in a uniform 1:1 allocation ratio (control: intervention). Randomization is based on a permuted randomized block design, where the strata are gender, age, and recruitment site. The randomized block method contained block sizes of 2 and 4 in a ratio of 2:1 to minimize imbalance in small strata groups. A randomization list was generated by an independent statistician using RandomiseR package [33] within the R computing environment (The R Foundation, Vienna, Austria). For each participant, the computer system automatically produces a study identification number, which will be used on all study documents. On the following Monday, after the baseline visit, the computer system automatically sends the assigned text message program to the participant. Therefore, the researcher conducting all face-to-face assessments remains blind to the study allocation. As an additional precaution and for safety purposes, there will be an independent, unblinded researcher monitoring all incoming text messages.

A 20% (30/150) subsample of participants will be randomly assigned to wear an accelerometer for seven days to validate the self-reported physical activity questionnaire. These participants will receive a second layer of randomization, which will be nested within each treatment arm at a ratio of 1:5. A total of 15 participants with accelerometers will be in the text message intervention group, and 15 participants will be in the control group.

### Study Population

Participants will be eligible to participate if they are: (1) 13 to 18 years old inclusive; (2) are overweight, defined by the International Obesity Task Force as equivalent to an adult BMI of 25.0-29.9 kg/m^2^ [34,35]; (3) own an operational mobile phone that is capable of sending and receiving text messages; and (4) provide written informed consent themselves or provide written informed consent from their parents or guardians (if <18 years old).

Participants will be excluded if they: (1) have a diagnosis of Type 1 diabetes or Type 2 diabetes; (2) have a medical condition or psychiatric illness that would not allow the participant to give informed consent or would preclude the participant’s ability to comply with the study protocol; (3) a history of disordered eating, including being diagnosed with, or treated for, Anorexia nervosa or Anorexia athletica, Binge Eating Disorder, or Bulimia nervosa; (4) are pregnant, or are planning to become pregnant within the next 12 months; (5) are on weight loss medications or any medications known to cause weight gain; (6) are enrolled in an alternative randomized weight management program; (7) are already participating in a text message-based study; or (8) cannot speak English. The team will keep recruitment and screening logs for those people who are ineligible or decline to participate, with basic demographic information and reasons for nonparticipation.

### Control Group

The control group will receive usual care. For this study, usual care is defined as accessing available health services and information for adolescent obesity prevention, as outlined in the clinical practice guidelines for overweight and obese adults, adolescents, and children in Australia [36]. Participants in the control group will receive an initial text message welcoming them to the study. However, they will not receive the text message support program or health counseling telephone calls. The control group will also receive a text message reminder approximately six- and twelve-months after their enrolment, notifying them that they will be contacted to schedule their six- and twelve-month follow-up visits, respectively. Participants in the control group will be offered the opportunity to receive the text message support intervention (no health counseling) at the end of the study (twelve-month visit) if they wish.

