Introductory	*Hi [pref_name]^a^, welcome to the TEXTBITES^b^ study. We hope you find the program fun and helpful. If you have any questions throughout the program, text us or call. We are here to support you! If you ever want to stop the messages, respond STOP to opt-out.*
Physical activity	*Need a dose of some happy hormones? Stretching can release endorphins, reduce your stress and make you feel great. The best part? You can do it anywhere, even while watching TV or YouTube. Check it out: tinyurl.com/stretchyout.*
Nutrition	*Corn isn’t just a tasty snack, it’s multi-purpose! It can be used to make fireworks, glue, paint & plastic. But let's face it, popcorn is one of the best uses, check out some recipe ideas here: tinyurl.com/airpopcorn.*
Mental wellbeing	*Your brain has 86 billion thinking cells (called “neurons”) & 80 billion or so supporting cells. Wow, that's a lot! No wonder they need a break at night to rest & recover. Make sure to give them 8-10 hours rest each day!*
General behaviors	*Want to get your homework or study done in record time? Do power bursts! Put your phone on do not disturb and power it out for 25 min. Take a 5 min break (yep, you can check your phone) and repeat until your work is done!*
Health counselor	*How is everything going, [pref_name]? Text back if you would like to chat with our health counsellor about all things food, exercise and wellbeing and we will get back to you soon.*
Final	*This is your last message from the TEXTBITES study. Thank you for being a part of the program, we couldn’t have done it without you! We will contact you shortly to arrange your 6-month follow-up interview. Thanks again from the TEXTBITES study team!*

^a^pref_name: participants preferred first name

^b^TEXTBITES: TEXT message Behavioral Intervention for Teens on Eating, physical activity, and Social wellbeing

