### Text Message Management System

The text message management system was developed in conjunction with the text message intervention to support women's physical and mental health after breast cancer treatments study and has similar processes [46]. Each week messages will be selected from the message bank by the software sequencer system that ensures that participants are receiving the correct messages (intervention vs control). Both intervention and control groups will receive a welcome text message at the beginning of the study and a concluding message at the end of the 6-months. Each text message will have a unique signature to ensure that participants know these messages are from the TEXTBITES study. All participants will be given brief training at baseline on how to read, delete, and save a text message, and how to unsubscribe if required. Training will also include safe and acceptable times to read the text messages (eg, reminding participants they must not read the text messages or use any other mobile phone functions if they are driving). All participants will also be provided with the research personnel’s contact details and will be contacted at least once during the intervention period to organize the six-month follow-up assessment and once during the follow-up period to facilitate the twelve-month follow-up assessment.

A researcher will manage a study mobile phone, and a record will be kept of any incoming messages from participants, and all out-going replies from the study health counselor throughout the study. Any analysis of these incoming text messages will be performed at the group level, except for reporting examples of individual quotes, which will be anonymized to protect the participant’s identity. Participants from either group can withdraw from the study at any time with or without giving a reason by replying “STOP” to any of the messages or contacting a member of the research team, which will activate a process of review and withdrawal from the study. If a reason for withdrawal is provided, it will be recorded.

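### Only the control arm is described as getting an advance text before the 12-month visit, while the intervention arm's month-six text calls itself the last message from the study

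*Protocol article*

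**What the plan says.** Three places in the protocol article bear on this.

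- **Control Group.** Controls receive a welcome text, and "The control group will also receive a text message reminder approximately six- and twelve-months after their enrolment". Each such text gives advance notice of a scheduling contact; it is not that contact.
- **Message Content, Frequency, and Sequence, with Table 1.** The intervention arm's final text, sent as the six-month program ends, states "This is your last message from the TEXTBITES study" and later adds "We will contact you shortly to arrange your 6-month follow-up interview". It does not mention the 12-month visit. No 12-month text for this arm appears here or elsewhere in the article.
- **Text Message Management System.** Each arm is to get a welcome text and, at month six, a closing one. The same section says that all participants will be contacted at least once during the intervention period about the 6-month visit, and "once during the follow-up period to facilitate the twelve-month follow-up assessment".

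On timing, the abstract states: "The primary outcome is a change in BMI *z* score at six months". Twelve months is follow-up, although the Discussion hypothesises a benefit there too, and Statistical Considerations applies the same models at both time points to all available data.

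**The concern.** Procedures that bring participants back for measurement should not depend on allocation. Here one arm is described as getting an extra prompt before the 12-month visit, and the other has been told six months before that visit that the study's messages are over. An intervention participant who takes that text literally could think that participation ends with the 6-month interview.

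The 12-month analysis uses whoever has data. If the prompting difference made attendance differ between arms, and if those who stay away differ in outcome from those who attend, the 12-month contrast would carry a component unrelated to the intervention. The trial already allows for 30% dropout in its sample size, so an avoidable difference in retention procedure is worth removing.

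**Working it through.** **1. Is the intervention-arm text list complete?** The message bank is itemised: 26 healthy eating, 18 physical activity, 21 mental wellbeing, 34 general, 6 health-counselor prompts, 1 welcome, 1 final.

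26 + 18 + 21 + 34 + 6 + 1 + 1 = 107, the stated total.

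So no 12-month notice is in the bank. One could be sent outside the bank, but it would contradict a closing text that says no more will follow.

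**2. The arms side by side.**

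| Step | Control | Intervention |
|---|---|---|
| Text about month 6 announcing contact for the visit | Yes | Yes (in the final text) |
| Contact to arrange the 6-month visit | Yes | Yes |
| Month-six text worded as the last from the study | Wording not given | Yes |
| Text about month 12 announcing contact for the visit | Yes | None described |
| Contact to arrange the 12-month visit | Yes | Yes |

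The arms match at six months. At 12 months the contact that books the visit is common to both. The difference is the advance notice, plus the documented closing wording.

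**3. The plan's own figure.** Inputs from Statistical Considerations: difference 0.15, SD 0.27, two-sided 5%, power 80%, dropout 30%.

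- Normal approximation: n = 2(1.96 + 0.84)² × 0.27² / 0.15², giving 51 per arm; 51/0.7 = 72.9, so 73 per arm, 146 in total.
- t-test: 51.8, so 52 per arm; 52/0.7 = 74.3, so 75 per arm, 150 in total, as stated.

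The sample size reproduces and is not in dispute.

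**4. Does unequal attendance by itself cost power?** No 12-month effect or SD is given, so this borrows the six-month values as an assumption, with 75 randomized per arm.

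| Dropout, control / intervention | Analysed | Power |
|---|---|---|
| 30% / 30% | 52.5 / 52.5 | 81.2% |
| 25% / 35% | 56.25 / 48.75 | 81.0% |
| 20% / 40% | 60 / 45 | 80.4% |

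With average dropout held at 30%, imbalance costs less than one percentage point of power. Any harm would have to come through bias.

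**5. What would bias require?** Within an arm, the attenders' mean minus the full-arm mean equals d × δ, where d is the fraction missing and δ is the attender-minus-non-attender difference left after adjustment. If δ is the same in both arms, the bias in the contrast is δ × (d_I − d_C). It needs both an attendance gap and a non-zero δ. The document gives neither.

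Purely as a scenario, assume gaps of 5 to 10 points (75 × 0.05 = 3.75 to 75 × 0.10 = 7.5 participants) and take the plan's 0.15 and 0.27 as yardsticks for δ:

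- low: 0.05 × 0.15 = 0.0075
- high: 0.10 × 0.27 = 0.027, which is 0.027/0.15 = 18% of the target difference

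These are assumed inputs, not estimates of what one text would do.

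**The case against.** The strongest case against is that the contact that matters is already symmetric: everyone is to be contacted to arrange the 12-month visit, and the control text merely announces that contact. Table 1 is labelled as examples, the 107-message bank is program content, and a condensed article may have left out a follow-up text for the intervention arm. The closing text can be read as closing the program rather than the study. The models adjust for the baseline outcome, and completers are to be compared with non-completers.

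Most of this stands, and it limits the point. It does not remove it: the extra notice is written for one arm only, and the closing text as quoted refers to the study, not the program. That wording is fixed in the article, not merely omitted from it.

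A reader might be tempted further, in ways the document does not support:

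- **That intervention participants get no prompt for the 12-month visit.** The contact planned for all participants rules this out.
- **That the primary result is affected.** At six months both arms are told by text to expect contact, and both are contacted.
- **That the article contradicts itself on a concluding message for controls.** Their six-month text can be that message.
- **That the six-month texts are timed unequally.** Control texts are timed approximately from enrolment, and the program starts the Monday after the baseline visit. The offset is probably a matter of days.

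**Conclusion.** The point holds in a limited form. As written, the arms differ before the 12-month visit by one advance-notice text and by a month-six message telling the intervention arm that it has had its last text from the study. Only the secondary 12-month comparison is exposed.

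A reader might infer that this will produce differential attendance and a biased 12-month effect. The document does not show that. It gives no 12-month retention by arm, no effect of such a text on attendance, and no outcome difference between attenders and non-attenders. The 30% dropout belongs to the six-month sample-size calculation and says nothing about a difference between arms. The risk is therefore possible and unsized. The case for change rests on the principle of equal follow-up procedures and on the very low cost, not on a demonstrated bias. If the full protocol already sends the 12-month text to both arms, only the closing wording and the article's description need correcting.

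**What to change.** 1. Send the same advance-notice text before the 12-month visit to both arms, and say so in both the Control Group and Text Message Management System sections.
2. Reword the intervention arm's month-six text so that it is the last message *of the program*, and add that the team will be in touch again about the 12-month visit.

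The cost is one automated text per intervention participant (at most 75) and a wording change. No visits, staff, sample size or analysis need to change.
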